#### Content of the control group intervention

Participants assigned to the control group receive a structurally equivalent intervention to rule out the possibility that attention received from FORT-group facilitators and the social support received during the FORT-group sessions, rather than the FORT intervention itself, is responsible for the FORT intervention’s effectiveness. To this end, the control group sessions have a structure similar to the FORT but different content. Specifically, the control group receives six, weekly, 2 h sessions, delivered by two health care professionals. Although the sessions focus on the challenges of living with a cancer diagnosis, the six sessions comprise a general support group but do not include the unique ingredients of the FORT intervention. Nonetheless, the intervention and control groups possess common factors in equal measure such as length and number of sessions, and both led by two health professionals [58]. During the control group sessions, the following topics are discussed: (a) exploring what it means when you find out you have cancer, (b) coping with post-treatment symptoms and side effects, (c) challenges of living with a cancer diagnosis, (d) incorporating wellness into your daily life, (e) building a survivorship plan, and (f) managing transitions (from active treatment to resuming work and family life). While the group leaders are instructed to create a supportive atmosphere in which patients may share their worries about living with a cancer diagnosis, the therapists are instructed not to teach the linkages between emotions and behaviors. Specifically, in the control group, potential therapeutic ingredients found in the FORT intervention group, such as cognitive reframing, building coping skills, or exposure to participants’ worst fears are not introduced. Group leaders in the control group are instructed to use reflection and restatement when participants do introduce these topics DL Safer and EM Hugo [58]. Although the control group comprises specific weekly topics, the content, and flow of each session are not highly scripted, no homework is assigned, and no relaxation exercises are taught during the sessions or practiced at home. The group leaders are expected to have clinical experience with cancer patients and general knowledge about the weekly topics.

#### Standardization and training in the FORT intervention and control intervention

To set performance standards and ensure treatment fidelity [59–61], we developed a FORT intervention manual and tested it in the pilot study for dosage (number of sessions) and intensity (duration of each session). After this pre-testing, the manual was refined for the RCT. All FORT facilitators receive the same 2-day training, under the direction of the first, second, third, and fourth authors, all of whom are well trained in Cognitive existential therapy. FORT leaders also attend annual, 1-day training refreshers to maintain their competency and to avoid therapist drift-off (e.g., expanding the session content based on insights from their clinical experience). We used this approach to monitoring treatment integrity and fidelity successfully in our pilot study.

Two specific control group leaders, with previous experience in delivering support groups to women with cancer, were asked by the research team to develop a manual for group leaders and participants, based on six established topics for the control group. The two control-group leaders did not participate in the FORT intervention training, to reduce risk of content contamination, and they provided training to group leaders at the other intervention sites. Analogous quality-control fidelity checks for reliability and consistency are done on both intervention and control groups.

All group sessions are audio-recorded and reviewed, with participants’ permission. The audio-recording are accessible only to the research team. The first and second authors independently and randomly review 20 % of all recordings, using fidelity checklists built from each of the intervention manuals. The checklists have two ratings: (a) areas covered (yes or no) and (b) quantity and quality of area covered (0–2). The second rating assesses adherence to the manuals, adequate processing of affect in the FORT intervention, and efficient time management. When adherence to the manuals is less than 80 %, the first and second authors review with group leaders how to improve adherence.

### Pilot study of the intervention

The pilot study of the FORT intervention was carried out between October 2010 and October 2012, with funding from the Canadian Institutes of Health Research [26, 27]. The pilot study assessed the feasibility and preliminary efficacy of the FORT intervention for 56 participants with either BC or GC. Briefly, we found that the intervention was feasible and showed promising efficacy. Specifically, women who took part in the intervention reported significant reductions in the primary outcome, FCR, and the secondary outcomes uncertainty, coping, cancer-specific distress, and quality of life, as measured before and immediately after the intervention. These changes were maintained 3 months after the intervention ended. Our RCT builds on the findings of the pilot study by comparing the FORT intervention to a structurally equivalent control group. In planning the RCT, we carefully took into account the issues found in the pilot study. First, although most psychological measures showed improved outcomes, we observed changes on only four of the 14 coping subscales, This result may suggest that the coping scale we chose for the pilot study may not have been specific enough to measure changes in other coping behaviours such as for cognitive avoidance, reassurance seeking, body checking that we had aimed to reduce, as based on our theoretical FCRM [27]. For the RCT, we, therefore, revised our coping measures to align them more closely with our theoretical model. Second, in the pilot study, we used an FCR measure that did not have a validated cut-off score for identifying clinically significant levels of FCR. Recent developments in psychometrics have made it possible to distinguish survivors with minimal FCR from those with clinical levels of FCR [11]. Consequently, for the RCT, we changed our measurement of FCR scale to a more reliable scale, the Fear of Cancer Recurrence Inventory, which has a validated clinical cut-off score based one of its subscales, the FCR severity scale [9]. The scale also provides a total FCR score [9]. We also reorganized the content of the weekly sessions, based on participants’ feedback [26]. One example was moving the nurse specialist’s presentation on cancer screening follow-ups from Session 2 to Session 3, to allow participants to learn coping skills for confronting anxiety associated with hearing about cancer risk. Finally, in the pilot study whereas therapeutic gains were not assessed beyond 3 months, the RCT includes a 6-month follow-up measurement.

### Primary and secondary outcomes in the RCT

The theoretical model for our pilot study guided the choice of measures included in the RCT questionnaire package. There are four measurement time-points for participants randomized to either the intervention or the control group: 2 weeks before the intervention (T1) 1 week after the intervention (T2), and 3 and 6 months after the intervention ends (T3 and T4, respectively). The first questionnaire package (T1) includes additional measures to evaluate the intervention and control groups’ comparability, such as demographic data including age and socioeconomic status, and medical history of cancer diagnosis.

The primary outcome of the study, *fear of cancer recurrence*, is measured by the Fear of Cancer Recurrence Inventory (FCRI) [9]. This 42-item questionnaire includes a total score as well as seven subscales, measuring triggers, FCR severity, psychological distress, functional impairment, insight, reassurance, and coping strategies. A score of 13 or higher on the nine-item severity subscale (range 0–3) indicates a clinical level of FCR [62]. The FCRI has been shown to have adequate reliability and validity (construct validity *r* = 0.68 to 0.77; reliability scores α = 0.95) [9].

The secondary outcomes are measured as follows: *Cancer-specific distress* is measured by the Impact of Event Scale (IES) [47], a 15-item questionnaire that assesses cancer distress. The IES has two subscales: intrusive thoughts and avoidance. The scale has good internal consistency (α = 0.84–0.91) and satisfactory test-retest reliability (total *r* = 0.80) [63]. *Perceived risk of cancer recurrence* is measured by a single-item question asking respondents to indicate their level of perceived personal risk for cancer recurrence over the last two days [64]. *Intolerance of uncertainty* is measured by the Intolerance of Uncertainty Scale (IUS) [65]. The IUS is a 27-item, four-factor questionnaire that presents uncertainty as stressful and upsetting, uncertainty as leading to the inability to act, uncertain events as being negative and to be avoided, and being uncertain as unfair [65]. The IUS has a reliability coefficient of *r* = 0.74 [65]. *Uncertainty in Illness* is measured by the Mishel Uncertainty in Illness Scale–Community version [56], which consists of 23 items rated on a five-point Likert scale. For cancer, this scale has alpha coefficients of 0.90 [66]. *Coping* is measured by the following three coping scales: (a) *Cognitive Avoidance Questionnaire* [67], a measure of avoidance coping of 25 items, (b) the *Reassurance-Seeking Behaviours subscale* of the Health Anxiety Questionnaire [68], a measure of body-checking and seeking reassurance of 3 items, and (c) the *Reassurance Questionnaire* [69], a measure of seeking reassurance from physicians of 10 items These coping measures have been extensively used for cancer patients as well as with other patients who have health anxiety. The measures have demonstrated satisfactory reliability and validity [56, 67, 70, 71]. *The quality of life* is measured by the SF-8 instrument [72], a health-related quality of life measure that assesses general physical and mental health within a 4-week recall period. Cronbach’s alpha internal consistency for both subscales is 0.61-0.68 [73].

#### Potential covariates

As group cohesion may influence the intervention’s impact, we measure group cohesion at the end of each 6-week FORT-intervention group and each 6-week control group intervention. Cohesion is measured using the *Group Cohesion Scale − Revised* [74], a 25-item scale measuring interaction and communication among group members. For example, one item is “Group members usually feel free to share information.” The Cronbach’s alpha internal consistency of this scale ranged from .77 to .90 during post-test assessment [74].

Group alliance within therapy groups can be therapeutic in and of itself and can enhance intervention efficacy [75]. That is, patients who perceive improvements during their therapy are more likely to have positive feelings towards the therapist, be more committed to treatment, and work more collaboratively. We measure group alliance using the *California Psychotherapy Alliance Scale* [76], a 24-item scale with four theoretically derived dimensions: (a) the therapeutic alliance, (b) the working alliance, (c) the therapist’s contribution to the alliance, and (d) the agreement on goals and tasks of therapy. We measure therapeutic-working-group alliance immediately following the last sessions of both the intervention and the control groups.

Treatment credibility and participants’ expectancy for improvement are two additional variables that may contribute to alternative explanations of differences found between two compared conditions [77]. To assess credibility and expectancy to ensure initial equivalency between the FORT intervention and the structurally equivalent control group, we are using the *Credibility/Expectancy Questionnaire* (CEQ) [77]. The CEQ has 6 items; three items relate to the credibility factor (“think” questions), and three items relate to the expectancy factor (“feel” questions). Each factor demonstrates high internal consistency (α = 0.81 for expectancy and α = 0.86 for credibility) and a good Cronbach’s alpha for the whole scale (α = 0.85) [77]. Test-retest reliability over a 1-week period scored at 0.82 for expectancy and 0.75 for credibility [77]. The CEQ has two ratings; one is from 1 (not at all) to 9 (very much), and the other from 0 % (not at all) to 100 % (very much). Scoring involves transforming the percentage to a number between 1 and 9, giving both scales a range from 3 to 27. The CEQ is given to participants immediately after the end of Session 1, in which the study intervention is explained. Both the FORT intervention and the control group members complete this scale.

#### Sample size

The primary study outcome is FCR, as measured by the FCRI [9]. The sample size was calculated based on the moderate changes in FCR we observed in the pilot study from baseline (T1) to 3 months post intervention [27] and in the only published RCT intervention study that addresses the fear of disease progression [78]. A sample size of at least 112 participants ensures our ability to detect an effect size of 0.40, with a power of 0.95 and an alpha level of .05 between pre- and post-intervention FCR measures. Therefore, we plan to recruit eight groups of seven participants, for a total of 56 participants per arm. We are also enrolling an additional two participants per group per arm, to account for possible dropouts (72 per arm). This strategy will yield 144 participants in total.

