**Methods:**

Sixteen groups of seven to nine women are being allocated to the intervention or the control group. The control group receives a 6-week, 2 h, structurally equivalent support group. We are recruiting 144 cancer survivors from four hospital sites in three Canadian cities. The sample size was based on the moderate pre/post-test changes found in our pilot study and adjusted to the drop-out rates. *Measurements*: The primary outcome, FCR, is measured by the Fear of Cancer Recurrence Inventory. Secondary outcomes measured include cancer-specific distress, perceived risk of cancer recurrence, illness uncertainty, intolerance of uncertainty, coping, and quality of life. We use reliable and recognized valid scales. Participants are to complete the questionnaire package at four times: before the first group session (baseline), immediately after the sixth session, and 3 and 6 months post-intervention. *Analysis*: In the descriptive analysis, comparison of group equivalent baseline variables, identification of confounding/intermediate variables and univariate analysis are planned. Each participant’s trajectory is calculated using Generalized Estimating Equation models to determine the time and group effects, after considering the correlation structures of the groups. An intent-to-treat analysis approach may be adopted.

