### Previous counseling approaches to fear of cancer recurrence

While there are several ongoing trials of FCR interventions [28–30], to date only one published intervention trial has addressed fear of disease progression, a concept related to FCR, in people with cancer or chronic arthritis [31]. This intervention involved both a cognitive behavioral group and a supportive-expressive group, and it successfully decreased fear of disease progression compared to a control group. However, all cancer participants were inpatients admitted to a rehabilitation clinic, and 20 % of them had recurrence or metastases. Hence, the concept of fear of disease progression addressed in this intervention may be more applicable to in-patients with active or advanced disease than to out-patients and those in remissions or with early-stage disease. Another intervention has been developed to address FCR among head-and-neck-cancer patients [32], but results of this trial have not yet been published.

Four additional studies evaluated group therapies designed to improve general psychological wellbeing outcomes for breast cancer survivors and reported on FCR as a secondary outcome. The first study evaluated the impact of a 6-session Mindfulness-Based Stress Reduction (MBSR) group and found a significant decrease in FCR immediately following the six sessions [33]. However, no follow-up study was conducted to evaluate the long-term effectiveness of the intervention, and the study did not include an attention only control group. The second study reported similar findings from an 8-session MBSR group [34] but, again, the study did not include an attention only control group, and the sample was small. The third study reported significant reductions in FCR immediately following a 12-week Emotion Regulation Group [35]. However, improvements in FCR were not sustained at 6 and 12 months after the intervention. Fourth, a telephone intervention designed to improve communication between breast cancer survivors and their physicians did not decrease FCR (the secondary outcome), although the intervention did improve the primary outcome, self-efficacy [36].

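### The 0.40 effect and 0.95 power are stated for pre/post change, not for FORT versus the support group, and no allowance for control-arm improvement is shown

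*Protocol article*

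**What the plan says.** The Sample size section gives two sources for the planning effect. The first is the pilot: "The sample size was calculated based on the moderate changes in FCR we observed in the pilot study from baseline (T1", continuing to 3 months after the intervention. The second is change seen "in the only published RCT intervention study that addresses the fear of disease progression". The Methods part of the abstract names only the first: "The sample size was based on the moderate pre/post-test changes found in our pilot study". The section then says that at least 112 women allow the trial to "detect an effect size of 0.40, with a power of 0.95 and an alpha level of .05 between pre- and post-intervention FCR measures". That becomes 56 per arm, and 72 per arm (144 in all) after adding two women per group for dropout.

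The section on the pilot reports change before and after the intervention in women who took it, and says the present trial builds on this by adding a structurally equivalent control. It also says of the outcome measure that "we changed our measurement of FCR scale to a more reliable scale". The section on previous counseling approaches describes the published trial as involving "both a cognitive behavioral group and a supportive-expressive group, and it successfully decreased fear of disease progression compared to a control group".

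The research question is FORT compared with the structurally equivalent control. The section on the control intervention says that this arm exists to rule out attention and social support as the explanation of any benefit, and that "the six sessions comprise a general support group but do not include the unique ingredients of the FORT intervention".

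**The concern.** Two different quantities are in play. One is the change from baseline in women who receive FORT. The other is how far that change exceeds the change in women who attend a support group of the same length. The sample size is justified by the first, and the trial tests the second.

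A change from baseline in treated women contains whatever attention and group support contribute, which the control is designed to subtract. It also contains any natural improvement. In this trial, entry requires an FCRI severity score of at least 13 and an IES score of at least 24, so some fall from baseline can be expected in both arms through regression to the mean. Unless control women do not improve at all, the between-arm difference is smaller than the change in the FORT arm.

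The published trial does not supply the missing figure. It tested other interventions against its own control group, and nothing in the article says that this control resembled the support group used here.

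At stake is how the result is read. A non-significant comparison in a trial advertised as having 0.95 power invites the conclusion that FORT adds nothing to support, although the trial may have had modest power for a worthwhile addition. Correcting the power calculation alone does not settle this if 0.40 is kept without a between-arm reason.

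**Working it through.** **Inputs from the Sample size section.** Effect 0.40, treated here as standardised; power 0.95; alpha .05, sidedness not stated; 112 in total, 56 per arm. The SD, the pre/post correlation and the type of effect size are not given.

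**1. The stated figure.**
- As a paired pre/post test, two-sided, an effect of 0.40 needs 84 women in all for power 0.95. The noncentrality is 0.40 × √n; power is 0.84 with n = 56 and 0.99 with n = 112.
- As a between-arm test, n per arm = 2 × ((1.960 + 1.645)/0.40)² = 162.4, so 163 per arm (136 one-sided).
- Neither gives 112. A between-arm reading reaches about 56 per arm only with an unstated baseline correlation of about 0.81 (baseline-adjusted analysis) or 0.83 (change score).

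**2. The target under control-arm improvement.** Suppose that the support group achieves a share s of a 0.40 change in the FORT arm. The between-arm difference is then 0.40 × (1 − s). The documents give no value of s, so the range is an assumption: s = 0, 25%, 50% and 75% give 0.40, 0.30, 0.20 and 0.10 SD.

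**3. Power of 56 per arm for one follow-up, two-sided .05, no clustering.** Noncentrality = (d/k) × √(56/2), with 110 degrees of freedom. Here k = 1 unadjusted, and k = √(1 − r²) = 0.8 with baseline adjustment at an assumed r = 0.6. Example: 0.40 × √28 = 2.117, power 0.555.

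| Difference (SD) | Unadjusted | r = 0.6 |
|---|---|---|
| 0.40 | 0.56 | 0.75 |
| 0.30 | 0.35 | 0.50 |
| 0.20 | 0.18 | 0.26 |
| 0.10 | 0.08 | 0.10 |

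On the same assumptions, the difference detectable with 80% power is 0.53 SD unadjusted and 0.43 SD at r = 0.6. The 95% interval half-width is 0.37 and 0.30 SD.

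**4. Sensitivity to the follow-up contrast.** The Statistical analysis section plans GEE over T1 to T4. If the contrast were the mean of the three follow-ups, with equal correlations r and baseline adjustment, then k = √((1 + 2r)/3 − r²). At r = 0.6, k = √(0.733 − 0.36) = 0.611, and power at 0.40, 0.30 and 0.20 SD is 0.93, 0.73 and 0.40. At r = 0.5 it is 0.90, 0.68 and 0.37.

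**5. Sensitivity to clustering.** With seven women per group the design effect is 1 + 6 × ICC. Assumed ICCs of 0.01, 0.05 and 0.10 give 1.06, 1.30 and 1.60. Unadjusted single-follow-up power at 0.40 SD falls from 0.56 to 0.54, 0.46 and 0.39 (normal approximation).

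**The case against.** The strongest reply is that no overstatement has been demonstrated. The article calls the pilot changes moderate and then uses 0.40, without giving either source's effect. The 0.40 may already be a discounted value. This stands: a reader might infer that the pilot effect was carried over undiminished, or that 0.40 certainly exceeds the true difference, and the documents support neither. They show only that no discount is stated. The article's Background also reports that FCR tends to stay stable after treatment, which argues against a large natural improvement. It does not bear on what attention and group support contribute.

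Three further inferences are tempting and fail.
- **The published trial as proof that a supportive group works.** The article reports one overall benefit and no separate result for the supportive-expressive group. It does not say that the control was untreated, and that trial did not test FORT.
- **The change of scale and the remark about in-patients as evidence of overstatement.** A more reliable scale would, if anything, raise a standardised effect. The in-patient remark concerns applicability. Both weaken the link between the sources and this trial, but neither shows a direction.
- **A non-significant result as the likely outcome.** The single-follow-up figures at 0.20 SD suggest it, but at 0.30 SD and r = 0.6 power is already 0.50, and averaging follow-ups gives 0.73 before clustering.

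It can also be said that an article leaves the full derivation to the full protocol, and that nothing in it says a null result would be read as equivalence. Both are fair. But this article does not merely omit the derivation. It names the contrast that was powered, and that contrast is not the one in its research question.

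**Conclusion.** The point holds as a mismatch between the stated basis of the sample size and the comparison under test. The 0.40 and the 0.95 are attached to change from baseline; no between-arm effect against an attention- and support-matched control is given, and no allowance for improvement in that arm is stated. They are probably too favourable for the primary comparison, because a pre/post change includes components that the control removes. That is an expectation from the design and not a measured overstatement. Its amount cannot be computed from the article.

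The range in size depends on assumptions that the article does not fix: the share of change achieved by the control arm, the baseline correlation, whether one follow-up or an average is tested, and the ICC. That the pilot had no comparison arm is inferred from its description. The published trial carries different reference numbers in the two sections and is taken as one trial because both call it the only published one.

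**What to change.** In the Sample size section:
- State the target as a between-arm difference on the chosen FCRI score against the support group. Justify it either as the smallest difference worth having over support, or as the pilot change minus an explicit assumed control-arm change.
- Keep 144 women. Replace the 0.95 claim with the power, or the detectable difference, of 56 per arm for that contrast over a range such as 0.20 to 0.40 SD.
- State the assumptions behind those figures: sidedness, baseline correlation, follow-up contrast (one time point or an average) and the allowance for clustering by therapy group.

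A sentence saying that a non-significant primary result will be read from its confidence interval would guard against the misreading described above.

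The cost is rewriting one section, with no extra women or visits. The downside is that the stated power becomes less favourable.

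### The 95% power claimed for an effect of 0.40 with 112 women belongs to a pre/post contrast and does not carry over to the between-arm hypothesis the trial tests

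*Protocol article*

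**What the plan says.** The Sample size section names FCR on the FCRI as the primary outcome and states: "A sample size of at least 112 participants ensures our ability to detect an effect size of 0.40, with a power of 0.95". The test is set at the 5% level, and the contrast to which this power belongs is given as one "between pre- and post-intervention FCR measures". The section draws the effect size from two sources: the change seen in the pilot from baseline to 3 months after the intervention, and one published randomised trial on fear of disease progression. The abstract gives only the first: "The sample size was based on the moderate pre/post-test changes found in our pilot study".

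The 112 is then turned into a two-arm design: "we plan to recruit eight groups of seven participants, for a total of 56 participants per arm". Two extra women per group are enrolled to cover dropout, which makes 72 per arm and 144 in all.

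The Research question and hypotheses section sets the primary hypothesis as less FCR with FORT than with a structurally equivalent control group, with the difference maintained at T3 and T4. The Statistical analysis section plans GEE models over T1–T4, and the abstract says that the correlation structure of the groups will be considered. The Pilot study section describes before-and-after gains, presents the control comparison as what the RCT adds, and says of the FCR instrument: "we changed our measurement of FCR scale to a more reliable scale".

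**The concern.** A power figure is meaningful only for the contrast it was computed for. Here it is attached to change over time, whereas the trial is judged on a difference between two arms that both receive six group sessions. A between-arm difference has a larger standard error than a within-person change in the same number of women. It is also likely to be smaller than a pre/post change, because the control sessions are meant to share the attention and support components.

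What is at stake is how a null or imprecise result is read. A reader told that 112 women ensure 0.95 power for 0.40 would take a non-significant result as good evidence against a difference of that size. On most analyses the plan permits, the design does not support that inference.

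**Working it through.** **Inputs from the Sample size section:** effect 0.40 (metric not stated), alpha 0.05 (taken as two-sided), power 0.95, 56 per arm, eight groups of seven per arm. **Assumed, because the article gives neither:** baseline-outcome correlation r of 0.3 to 0.7, with the same r between all pairs of visits; intraclass correlation (ICC) within therapy groups of 0.02 to 0.10, applied to the residual variance. All powers use the noncentral t.

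**1. The stated figure, on its own pre/post contrast.** Paired test, noncentrality = δ√n.
- If 0.40 is in SDs of change: 83.7% with 56 women and 98.7% with 112; 95% needs 84 women.
- If 0.40 is in SDs of the raw score: δ = 0.40/√(2(1−r)). With 112 women, r = 0.33 gives δ = 0.346 and power 95.2%. With the 56 women of one arm, r = 0.67 gives δ = 0.492 and power 95.1%.

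So 0.95 can be reached on the pre/post contrast, but only with a metric and a correlation that the article does not state.

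**2. The between-arm contrast, unadjusted, one visit.** Noncentrality = 0.40/√(2/56) = 2.117, df 110: power **55.5%**. With all 72 per arm retained, noncentrality = 0.40/√(2/72) = 2.40: 66.4%. Power of 95% needs **164 per arm** (328 in total). Reading 0.40 as Cohen's f (a standardised difference of 0.80) would give 98.7% with 56 per arm, so that does not yield 0.95 either.

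**3. Allowing for the baseline and for repeated visits.** Noncentrality = 0.40/√(2V/56), where V is the residual variance in units of the raw SD squared:
- one visit, baseline-adjusted: V = 1 − r²
- mean of T2–T4, baseline-adjusted: V = (1 + 2r)/3 − r²

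| r | V, one visit | Power | V, mean of T2–T4 | Power |
|---|---|---|---|---|
| 0.3 | 0.910 | 59% | 0.443 | 88% |
| 0.5 | 0.750 | 68% | 0.417 | 90% |
| 0.7 | 0.510 | 84% | 0.310 | 96% |

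At one visit, 95% needs r of about 0.81 to 0.82.

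**4. Adding clustering by therapy group.** Multiply V by the design effect 1 + (7 − 1) × ICC and use 16 − 2 = 14 df.

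| ICC | Design effect | Unadjusted, one visit | Adjusted, one visit (r 0.3 to 0.7) | Adjusted mean of T2–T4 (r 0.3 to 0.7) |
|---|---|---|---|---|
| 0.02 | 1.12 | 46% | 50–74% | 80–92% |
| 0.05 | 1.30 | 41% | 44–68% | 74–87% |
| 0.10 | 1.60 | 34% | 37–59% | 65–80% |

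No cell reaches 95%.

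**5. Head-count.** 8 × 7 = 56, 8 × 9 = 72 and 2 × 72 = 144 are consistent with one another. The dropout allowance is not in dispute.

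**The case against.** Four points can be made for the plan, and each limits how far the criticism goes.

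- **The 0.95 is not shown to be an arithmetic error.** A reader might infer that no calculation gives it. Step 1 shows that a paired test in raw-score SDs does, at ordinary correlations. What stands is that it is the wrong contrast, with the metric unstated.
- **The planned analysis is stronger than an unadjusted one-visit test.** A reader might take 55% as the trial's power and conclude that a true difference of 0.40 would be missed about half the time. That holds only for some one-visit analyses. The plan is a GEE over four time points, and a baseline-adjusted mean of T2–T4 gives 88–96% before clustering. On the other side, the article does not commit to an averaged contrast, its hypotheses refer to T2, T3 and T4, and with clustering even that mean stays below 95% over the range examined.
- **The effect size does not rest on the pilot alone.** A reader might say that 0.40 is purely uncontrolled change inflated by regression to the mean. The Sample size section also cites a randomised trial, and the article does not show whether pilot women were selected for high scores. At most, the pilot part may include change that the control arm will share.
- **Clustering is not ignored.** The abstract promises to consider it in the analysis, and a condensed article may leave a design effect to the full protocol. Its absence from the sample-size text is weak evidence by itself. It matters here because the article says outright that 112 women ensure the power.

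**Conclusion.** The concern holds in this form: the article states 0.95 power for a pre/post contrast and presents it as the justification for a two-arm trial whose primary hypothesis is a between-arm difference, and the figure does not transfer. For a between-arm difference of 0.40 SD with 56 per arm, power is 55% unadjusted at one visit. Above that it depends on the analysis, on the baseline correlation and on the group ICC, as tabulated. Only the unclustered, baseline-adjusted T2–T4 mean at the upper end of the assumed correlations reaches 95%.

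The 55% and the 164 per arm follow from the article's own inputs with a two-sided test. Every other between-arm figure, apart from the 66.4% with 72 per arm, rests on assumed values of r, and of the ICC where clustering enters. The finding concerns a wrong statement of power. It does not show that the trial is too small to be worth running, nor that its head-count is miscalculated.

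**What to change.** Keep 144 recruited and 112 evaluable. In the Sample size section:

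1. Delete the statement that 112 participants ensure 0.95 power.
2. State power, or the detectable difference, for the FORT-versus-control contrast under the GEE analysis that will be run. Name the contrast (one visit, or an average over T2–T4), the effect-size metric and the sidedness.
3. Show a range over the assumed baseline correlation and group ICC, not a single pair of values, since the article supplies neither. The tables above can serve if no better values are available from the pilot.
4. State that 0.40 was based on pilot pre/post change measured on a different FCR scale and on a published randomised trial on fear of disease progression, and that the pilot part may include change that the control arm will share.

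Bring the abstract's sentence on the basis of the sample size into line. It gives no power figure, so only its description of the source needs rewording.

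The cost is rewording and a less favourable stated power. No patients are added, and allocation, endpoints and visits stay as they are.
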